### Randomisation

Following receipt of a “Welcome” SMS text-message confirming trial registration on the system, participants are randomised using a secure, remote, web-based computer schedule within one week of recruitment. A minimisation procedure, overseen by an independent statistician, is used to dynamically adjust randomisation probabilities minimising chance differences in gender (male, female), age (<55 years, ≥ 55 years), baseline systolic blood pressure (<140 mmHg, ≥ 140 mmHg), years with hypertension (< 10 years, ≥ 10 years), and previous clinic attendance (regular, irregular, unknown) between the groups. Research staff and clinic staff remain blind to the allocated treatment group.

### Data collection and management

We used software platforms that are non-proprietary, open-source, stable and widely available to deliver the mobile-phone based intervention at scale in a low-resource setting. We selected software that was easily customisable and suitable for use by non-technical field staff. Patient data is collected by fieldworkers using Internet-enabled mobile phones (HTC Wildfire S, HTC Corporation, Taiwan, Android OS 2.3.5) and tablet computers (Motorola Xoom, Motorola Corporation, Illinois, Android OS 4.0.4). Data entry is through on-screen case report forms developed using the open-source mobile-device application Sana Mobile (Sana, MIT, Massachusetts). The medical record is held in OpenMRS version 1.6.1 (OpenMRS, Limited, Michigan). OpenMRS is an open-source client–server software platform initially designed as an electronic medical record and health system management platform for low-resource settings. The database uses a “concept dictionary” which stores the terms describing each data variable. It is accessible through a web-based interface and the platform allows the development, upload and installation of custom-coded modules into the main framework enabling seamless interactivity with Sana Mobile. Participant blood pressure readings are transferred directly from the sphygmomanometer to the tablet computer using a Bluetooth™ protocol. Data are then securely transferred to a dedicated mobile dispatch server (MDS) using SSL transport layer encryption (data are uploaded incrementally to handle intermittent data connectivity). The MDS then compiles and uploads all the information to an individual patient electronic medical record in OpenMRS.

Data collected using Sana Mobile are error-checked using range and logic checks built into Sana at time of collection. All other data uploaded directly to the database, such as patient appointment attendance, are error-checked by the OpenMRS software before integration on the server. These include data format and range checks, appointment date checks and alignment between uploaded and existing data. The database is regularly backed up and password-protected, with differing levels of access for different research staff.

### Statistical methods

#### Analysis of primary and secondary outcomes

The primary statistical analysis will be carried out on an intention-to-treat (ITT) basis. We will endeavour to obtain full follow-up data on every participant to allow a full ITT analysis. The results from the trial will be reported as comparative summary statistics (difference in response rate or means) with 95% confidence intervals. All statistical tests will use a 5% two-sided significance level. The trial results will be reported in accordance with the CONSORT (Consolidated Standards of Reporting Trials) 2010 statements. A full detailed analysis plan (including plans for subgroup analysis and sensitivity analysis) will be prepared and finalised before unblinding of the data.

We will analyse the primary outcome (change in systolic blood pressure at 12 months from baseline) using a mixed-effects model on data collected at 6 and 12 months. An interaction between time and randomised group will be fitted to allow estimation of treatment effects (i.e. informational versus usual care, and interactive versus usual care) at each time point. The model will adjust for baseline systolic blood pressure and minimisation factors.

The secondary outcome measure of adherence will be dichotomised with a threshold of 80% (of days covered) to determine the proportion of participants judged adherent to medication. We will use chi-squared tests to examine differences between allocated groups.

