### Setting

Participants are recruited from the Vanguard Community Health Centre, a public sector, large primary care clinic in Bonteheuwel, Cape Town, South Africa, serving two diverse low-middle income communities, Langa and Bonteheuwel. The health centre provides a full range of primary care services with approximately 28,000 people attending each month. The “chronic diseases of lifestyle clinic” services a caseload of about 500 patients per week. Patients with hypertension are managed by nurse practitioners and doctors in structured clinics. The local Department of Health provides medications for the treatment of hypertension in line with national and international hypertension management guidelines [17]. Medications are provided either pre-packed from an off-site pharmacy, or dispensed on-site. Medications are usually provided for 28 days. Patients are required to attend the clinic monthly to collect their medication. There is no fee for receiving care or medication in primary care.

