#### Secondary outcomes

Treatment adherence is assessed by calculating the proportion of days of medication covered from routinely collected prescribing and dispensing data obtained during the 12-month follow-up period [24]. Data will be reported in three-monthly intervals. Adherence will be reported as the proportion of patients with ≥80% of days covered with medication [25], and as a continuous measure.

Additional secondary outcomes are: proportion of participants achieving a systolic blood pressure less than 140 mmHg and a diastolic blood pressure less than 90 mmHg, and health status measured with the EuroQol 5-Dimension and Visual Analogue Scale measures [26], proportion of scheduled clinic appointments attended, retention in clinical care, satisfaction with clinic services and care using 12 five-point Likert-scale items adapted from locally appropriate questionnaires developed to capture patient satisfaction with services for HIV-care, [27,28] hospital admissions, a Visual Analogue Scale for self-reported adherence to medication, and an adapted four-point scale evaluating basic hypertension knowledge. [29] We are also collecting data on the number and type of medication changes made during the trial and reported side-effects of medication. Anonymised demographic data are collected on non-participants.

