#### Sub-group analyses

We will carry out sub-group analyses of the primary outcome, systolic blood pressure and the main secondary outcome, adherence over last three months, by age (<50 years, ≥50 years), sex (male, female), number of years with hypertension (<1, 1–5, >5), baseline blood pressure (>140, ≤140 mmHg), presence of one or more co-morbid conditions, and self-reported adherence at baseline.

Missing data will be reported with reasons given where available and the missing data pattern explored. We will explore the mechanism of missing data, though the mixed-effects model does implicitly account for data missing at random.

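### The adherence test ignores the minimisation factors that the primary model adjusts for, so it is conservative and gives up power to an extent the protocol does not let us fix

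*Protocol article*

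**What the plan says.** The Randomisation section of the protocol article describes minimisation on gender, age, baseline systolic blood pressure, years with hypertension and "previous clinic attendance (regular, irregular, unknown) between the groups".

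Under Analysis of primary and secondary outcomes, the primary mixed-effects model takes account of this: "The model will adjust for baseline systolic blood pressure and minimisation factors". The next paragraph dichotomises adherence at 80% of days covered and then states: "We will use chi-squared tests to examine differences between allocated groups". No covariates are named for that test, and the article gives no adjusted or stratified analysis of adherence elsewhere.

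The Sub-group analyses section shows the standing of this outcome by calling it "the main secondary outcome, adherence over last three months".

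Two further statements bear on whether the factors matter for adherence. The Setting section says: "Patients are required to attend the clinic monthly to collect their medication". The Secondary outcomes section says that adherence is assessed by "calculating the proportion of days of medication covered from routinely collected prescribing and dispensing data".

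**The concern.** The same section respects the allocation scheme for the primary outcome and ignores it for the main secondary one, without giving a reason.

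Minimisation forces the arms to be alike on the chosen factors, so those factors add almost nothing to the chance difference between arms. A chi-squared test computes its standard error as if allocation had been simple randomisation, so it still counts that variation. If the factors predict the outcome, the standard error is too large, the p-value too high and the interval too wide.

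One factor is close to the outcome. Days covered are counted from dispensing records, and medicine is dispensed at monthly attendance, so a patient's past attendance record resembles a baseline version of the outcome. Adherence is what the text messages are meant to change. A needless loss of power here could leave a real effect short of significance.

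**Working it through.** **Inputs from the protocol.** Two-sided 5% level for all tests; 1215 participants, 405 per arm; five minimisation factors, one of them with three levels. The sample size section is powered on systolic blood pressure only. No expected adherence rate, effect or power is stated for adherence, so the only plan figure to reproduce is the nominal 5%.

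**Input that is not in the protocol.** R², the share of variance in the adherence outcome explained by the minimisation factors. I treat it as an assumption and vary it.

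**Formulas.** With the factors balanced, the unadjusted test statistic has null variance of about 1 − R² instead of 1. Then:

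- true alpha = 2 × [1 − Φ(1.96 / √(1 − R²))]
- where the adjusted test has 80% power, its mean is 1.96 + 0.8416 = 2.8016, and the unadjusted power is Φ(2.8016 − 1.96 / √(1 − R²))
- the unadjusted interval is too wide by a factor of 1 / √(1 − R²)

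| R² | 1.96 / √(1 − R²) | True alpha | Unadjusted power (adjusted = 80%) | Interval too wide by |
|---|---|---|---|---|
| 0 | 1.960 | 5.0% | 80.0% | 0% |
| 0.02 | 1.980 | 4.8% | 79.4% | 1% |
| 0.05 | 2.011 | 4.4% | 78.5% | 3% |
| 0.10 | 2.066 | 3.9% | 76.9% | 5% |
| 0.20 | 2.191 | 2.8% | 72.9% | 12% |

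The first row returns the plan's nominal level, as it should when the factors carry no information.

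**What such R² values would mean.** Take previous attendance alone, with assumed shares of 50/35/15% for regular/irregular/unknown.

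- Assumed adherence 75/40/55%: overall rate 0.5975. Between-category variance is 0.5 × 0.1525² + 0.35 × 0.1975² + 0.15 × 0.0475² = 0.0256. Total variance is 0.5975 × 0.4025 = 0.2405. R² is about 0.107 and true alpha about 3.8%.
- Assumed adherence 80/30/55%: overall rate 0.5875, between-category variance 0.0517, total variance 0.2423. R² is about 0.213 and true alpha about 2.7%.

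The upper end of the table therefore needs a large gap between regular and irregular attenders.

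**Check by simulation.** 1215 participants were minimised 1:1:1 on the five factors, with 3000 runs per scenario. One active arm was compared with usual care by chi-squared and by logistic regression on arm plus the factors. Assumptions: 80% biased allocation (otherwise random among the three arms), overall adherence of about 60% to 70%, treatment log odds ratio 0.45, no loss to follow-up.

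| Strength of factors | Alpha, chi-squared | Alpha, adjusted | Power, chi-squared | Power, adjusted |
|---|---|---|---|---|
| None | 5.1% | 5.1% | 84.7% | 84.8% |
| Weak | 4.9% | 5.1% | 85.6% | 85.8% |
| Moderate | 4.5% | 5.0% | 79.7% | 80.9% |
| Strong | 3.0% | 4.7% | 70.4% | 76.6% |

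The Monte Carlo standard error for alpha is about 0.4 points. The moderate value of 4.5% is not clearly below 5% on its own, but it agrees in direction with the formula. The adjusted analysis stays near 5% throughout and costs nothing when the factors are uninformative.

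**The case against.** The best case for leaving the plan alone has four parts.

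- **The test is safe.** A reader might infer from a wrong error rate that false positives are inflated or that the estimate is biased. Neither follows. The error runs in the conservative direction only. This stands in full.
- **The size is unknown.** The documents give no adherence rates, no category shares and no association. Attendance has an unknown level, and patients about to start medication are eligible; for both groups past attendance may say little about later collection. With weak prediction the loss is negligible. This also stands: a material loss is plausible, not shown.
- **Other adherence results are planned.** The Secondary outcomes section also reports adherence as a continuous measure and in three-monthly intervals, so the dichotomised test is not the only evidence. This softens the consequence but leaves the named test as it is.
- **A full analysis plan is promised before unblinding.** Adjustment could be settled there, and its described contents are not exclusive. But the article does not leave the method open: it names the test, one paragraph after adjusting the primary model.

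Two stronger readings are tempting and should not be drawn. One is that a single three-group test is planned, which would answer neither comparison with usual care. The text speaks of tests in the plural and, for the primary model, names each intervention against usual care, so pairwise tests are a natural reading. The other is that no effect size will be given. The same section promises differences in response rates or means with 95% confidence intervals for the trial results. What remains is that such an interval, if unadjusted, is too wide for the same reason as the test.

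**Conclusion.** The point holds as one of efficiency and consistency, on the main secondary outcome only. The protocol fixes an unadjusted test after minimised allocation, while it adjusts the primary analysis for the same factors. The result is a conservative test and interval.

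Over an assumed R² of 0.02 to 0.20, the loss is about 0.6 to 7.1 percentage points of power where the adjusted test has 80%. In the simulated scenarios it ran from about 0 to 6 points. These figures rest on the assumed strength of the factors, near-complete balance from minimisation and, in the simulation, the assumed factor frequencies and allocation probability.

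I am confident of the direction. I am not confident that the loss is large in this trial, because the one quantity that decides it is absent from the documents. The primary analysis is unaffected.

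**What to change.** Make the main adherence analysis a logistic model for at least 80% of days covered, with arm and the same minimisation factors as the primary model. From it, report the adjusted risk difference by marginal standardisation, with 95% CI, for the informational arm against usual care and for the interactive arm against usual care. Keep the crude proportions and the chi-squared test as descriptive or supporting results.

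The cost is a change of wording in the analysis section or in the promised analysis plan, made before unblinding. All the covariates are already collected for randomisation. Sample size, data collection and the primary analysis do not change.

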#### Sub-group analyses

We will carry out sub-group analyses of the primary outcome, systolic blood pressure and the main secondary outcome, adherence over last three months, by age (<50 years, ≥50 years), sex (male, female), number of years with hypertension (<1, 1–5, >5), baseline blood pressure (>140, ≤140 mmHg), presence of one or more co-morbid conditions, and self-reported adherence at baseline.

Missing data will be reported with reasons given where available and the missing data pattern explored. We will explore the mechanism of missing data, though the mixed-effects model does implicitly account for data missing at random.

### Reporting of adverse events for this trial

Reporting of serious adverse events will be limited to events not already listed as primary or secondary outcomes, but which might reasonably occur as a consequence of the trial. Additionally we will record adverse events that might be reasonably related to SMS text-messaging including hand or finger pain, or involvement in an accident as a result of sending or receiving a text.

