#### Informational (unidirectional) SMS text-message system

Participants allocated to the informational SMS text-message group receive an intervention that includes reminders about medication collection, scheduled clinic appointments and follow-up text-messages (including reminders when medicines are not collected), and a SMS-text promoting specific adherence-related behaviours. The SMS-texts are sent weekly at a time and in a language selected by the participant. Some of the texts are personalised (include first or chosen name). The intervention is compliant with South African regulations and ethics, and regulatory guidelines on good SMS-practice [21].

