#### Interactive (bidirectional SMS text-message reminders)

In addition to the intervention provided to participants allocated to the informational SMS text-message group, participants in the interactive SMS text-message group can also respond to texts and send messages to the clinic. For example, when appointment reminders are sent to participants in the interactive SMS text-message group, they will include an option to reply if they cannot make their scheduled appointment and to cancel or change their appointment as necessary. Examples of the type of SMS text-messages sent to participants allocated to the two intervention arms are shown in Table 2.

**Table 2 T2:** Examples of intervention group SMS-text messages in English

• **Appointment reminder SMS-texts**	*Hi [insert name]. Pls remember your next MEDICINE DATE is on [DAY][DD/MM/YY] at [TIME]. Thnx Dr [NAME] (DR@VAN)*
• **In response to missing a scheduled appointment**	*We missed you @ PHARMACY. We hope you’re OK. Pls be sure to come in to collect your MEDICINE. Thnx Dr [NAME] (DR@VAN)*
• **Messages related to specific issues**	*A pill box can help you to remember when to take your high blood pills. Ask at PHARMACY where you can buy one. Thnx Dr[NAME](PHARM@VAN)*
	*Pls be sure to take all your medicine as directed even if you feel well. Thnx Sr [NAME](SR@VAN)*
	*Pls tell us(DR&PHARMACY)if you think your high blood pills are making you feel unwell. Ask us about common side effects of your pills. Thnx Dr [NAME](DR&PHARM@VAN)*

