#### Usual care

Participants allocated to the usual care group only receive the SMS-texts sent to all trial participants. These messages are sent no more frequently than one SMS text-message every four weeks. The messages are a welcome SMS text-message, a text confirming enrolment, an SMS text-message on a birthday, and other SMS text-messages about participation in the trial. Examples of the types of SMS texts-messages sent to all trial participants can be seen in Table 3.

**Table 3 T3:** Examples of trial-specific group-text messages in English

**• Welcome SMS-text message**	*Welcome to StAR* thank you for participating. The trial cell is 0XXXXXX120 (save on phone). We will never ask for personal or banking details. Dr[NAME](StAR*@VAN)*
**• Trial specific SMS-texts**	*Pls remember your participation in StAR* is voluntary. Call, text, or send plz cal 0XXXXXX372 (its free) if you need to withdraw. Thnx Dr [NAME] (StAR*@VAN)*
	*Pls remember participating in StAR is free. We do not charge you for the SMS-texts we send to you. Thnx Dr [NAME] (StAR@VAN)*
**• Birthday SMS-text**	*Hi [NAME]. Happy birthday, have a great day. Thnx [NAMES](Health Team & StAR*@VAN)*

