#### Follow up to 12 months

Trial participants are followed upwhen they attend for planned clinic appointments. Data on scheduled clinic appointment attendance, prescription refill collection, and drug availability are extracted from routinely collected service-delivery data. At the six-month visit participants have their blood pressure measured and their contact details updated if necessary. At the final twelve month follow-up, anthropometry is repeated and blood pressure measured, a follow-up questionnaire is administered by a research assistant and clinical records are reviewed to capture intervening clinical events and changes in medical management. Participants who miss their scheduled visit at 12 months are actively traced by community-based research staff; if cause for non-attendance is hospital admission or death, then hospital records or death certificate data are obtained.

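### Accidents are recorded only if linked to a text, so the attributed count is not an unbiased comparison between arms that are sent different numbers of texts

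*Protocol article*

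**What the plan says.** The section on reporting of adverse events has two rules. Serious adverse events are reported if they are not already trial outcomes "but which might reasonably occur as a consequence of the trial". For other events, the protocol states that "we will record adverse events that might be reasonably related to SMS text-messaging", and names as examples "hand or finger pain, or involvement in an accident as a result of sending or receiving a text".

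Exposure to texts differs by arm. For the informational arm: "The SMS-texts are sent weekly at a time and in a language selected by the participant". The interactive arm gets the same programme and in addition "participants in the interactive SMS text-message group can also respond to texts and send messages to the clinic". For the messages that go to all participants, which are the only ones usual care receives: "These messages are sent no more frequently than one SMS text-message every four weeks".

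The Randomisation section keeps research and clinic staff blind to allocation. Participants see their own messages, and the section on intervention fidelity says they are told that message numbers and types vary.

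Two other sources of events carry no stated attribution condition. Hospital admissions are a secondary outcome, and clinical records are reviewed at 12 months for intervening events. At that same visit "a follow-up questionnaire is administered by a research assistant".

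**The concern.** An accident enters this record only if somebody decides that a text caused it. The chance of making that link can depend on how many texts the person receives and sends, and that is what the trial randomises. Two errors follow, in opposite directions:

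- **No true harm.** An active-arm participant has more texts near in time to any given accident, so coincidence alone can give a higher attributed count.
- **True harm that nobody notices as such.** If messaging raises accident risk but the participant does not connect the accident with a text, the accident is not recorded and the excess is missed. This does not depend on the ratio of text frequencies.

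If the attributed count is higher in the active arms, a reader cannot tell a real effect from coincidence, because the section plans no count of all accidents by arm. A later analysis plan cannot restore minor accidents that were never written down. At stake is the interpretation of one safety item, not the efficacy result.

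**Working it through.** The protocol gives no figure for adverse events, so there is nothing of its own to reproduce. The steps below bound the possible bias. Every accident rate, attribution window and background texting volume is an assumption.

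**1. Trial texts per year (from the Interventions section).**
- Active arms: one a week, about 52.
- Usual care: at most one per four weeks, 52 / 4 = 13.
- If the texts sent to everyone come on top of the weekly programme: 52 + 13 = 65 in the active arms.

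**2. Ratio of attributed accidents with no true harm.** Assume the same accident rate in every arm and attribution by closeness in time to a text. The ratio is then (active texts + b) / (13 + b), where b is the assumed number of other texts a year that could be blamed.

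| b | Ratio, 52 active texts | Ratio, 65 active texts |
|---|---|---|
| 0 (trial texts only) | 52/13 = 4.0 | 65/13 = 5.0 |
| 52 | 104/65 = 1.6 | 117/65 = 1.8 |
| 365 | 417/378 = 1.10 | 430/378 = 1.14 |
| 1825 | 1877/1838 = 1.02 | 1890/1838 = 1.03 |

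These ratios put usual care at its ceiling of 13. Fewer texts there would raise the b = 0 ratio, while the usual-care count in step 3 would fall further.

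**3. Absolute counts from coincidence, trial texts only.** Expected count = 405 × a × (texts × w / 8760), where 405 is the planned group size, a the assumed yearly accident risk, w the attribution window in hours and 8760 the hours in a year.

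| a | w | Usual care (13) | Each active arm (52) |
|---|---|---|---|
| 2% | 24 h | 0.3 | 1.2 |
| 5% | 24 h | 0.7 | 2.9 |
| 10% | 24 h | 1.4 | 5.8 |
| 5% | 1 h | 0.03 | 0.12 |

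For example, 405 × 0.05 × (52 × 24 / 8760) = 2.9. Even a ratio of 4 amounts to a few events per arm at most, and to almost none with a short window.

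**4. What an all-cause count would offer.** At assumed risks of 2% and 8%, one arm would yield 405 × 0.02 = 8 and 405 × 0.08 = 32 accidents. The 95% confidence interval half-width for a difference between two arms with equal risk is 1.96 × √(2a(1 − a)/405):
- a = 2%: 1.9 percentage points.
- a = 8%: 3.7 percentage points.

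By the usual normal approximation (two-sided 5%, 80% power, 405 per arm), such a comparison would detect a rise from 2% to 5.8% or from 8% to 14.2%. These are risk ratios of about 2.9 and 1.8. With 20% loss (324 per arm) they become about 3.2 and 1.9. The comparison would not depend on attribution, but it would be imprecise.

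**The case against.** The other side has a good case, and much of it stands.

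- **Scope.** A reader might infer that all of the intervention's own harms are filtered by attribution. The text does not support that. The general threshold is one of plausible relation to texting, and the causal phrase attaches clearly only to accidents. Hand or finger pain can be read as recorded whenever it occurs.
- **Built-in difference.** A reader might infer that the arms' counts must differ, and by a factor of four. That needs mistaken or coincidental attribution, and to trial texts alone. The wording says a text, not a trial text, and ordinary texting pulls the ratio toward 1. Where attribution is correct, an excess in the active arms is a real effect of more texting.
- **Other data.** A reader might infer that the trial cannot show harm at all. Hospital admissions and the record review gather more serious events in every arm whatever their cause. What remains uncovered is mainly accidents that lead to neither an admission nor a record entry.
- **Proportion.** Limiting collection to plausibly related events is a defensible choice for a low-risk intervention in a pragmatic trial. No primary or secondary outcome rests on this list, and the section plans no formal test between arms. An all-cause comparison would detect only large effects.
- **Condensed article.** Who attributes events, how they are elicited and what the questionnaire asks may be set out in a full protocol that is not shown.

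The last point does not remove the concern. The article itself states the recording rule for accidents, and that rule contains the causal condition. Staff blinding does not remove it either, because participants know their own message volume.

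**Conclusion.** The point holds for accidents. Because the definition requires a causal link to a text, and the number of texts differs by randomised arm, the attributed accident count is not an unbiased comparison. It also omits accidents that nobody links to a text.

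The size of the bias is unknown. With trial texts alone and usual care at its ceiling, the ratio under no harm is about 4 to 5. With realistic background texting it may be close to 1. Coincidental counts are probably a few per arm or fewer. All of this rests on assumed accident rates, windows and texting volumes. Serious accidents are partly covered elsewhere, minor ones are not, and the primary outcome is unaffected. The change is worth considering because it costs little, not because the present rule threatens the trial's main conclusion.

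**What to change.** Amend the section on reporting of adverse events as follows:

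1. Record any accident or injury during the 12 months in all three arms, whatever its presumed cause, with identical closed questions in the 12-month questionnaire.
2. Report all-cause counts by randomised arm with confidence intervals, and state that the comparison will be imprecise.
3. Keep perceived relation to a text as a descriptive sub-item, so that the attributed count is not lost.
4. State that hand or finger pain is likewise recorded whatever its presumed cause.

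The cost is two or three items in a questionnaire that is already administered, plus more unrelated events to tabulate. The change should be in place before the 12-month visits, since minor accidents not asked about then may not be recoverable.
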